## 2.5 Safety Outcome Measures:

Safety assessments will consist of monitoring and recording all adverse events and serious adverse events occurring during the regular monitoring of hematology and blood chemistry, ECG, regular measurement of vital signs, performance of physical and neurological examinations if needed.

## 3. STUDY DESIGN

This is an Open label, multicenter, randomized controlled clinical trial to evaluate the safety and efficacy of novel therapeutic agents in hospitalized adults diagnosed with COVID-19. It is a multicenter trial that will compare Favipiravir plus Hydroxychloroquine combination (experimental arm) to a control arm.

## 4. STUDY POPULATION

### 4.1 Inclusion Criteria

- 1 Should be at least 18 years of age,
- 2 Male or nonpregnant female,
- 3 Diagnosed with COVID-19 by PCR confirmed SARS-coV-2 viral infection.
- 4 Able to sign the consent form and agree to clinical samples collection (or their legal surrogates if subjects are or become unable to make informed decisions)..
- 5 Moderate or Severe COVID-19, defined as oxygen saturation (Sao2) of 94% or less while they were breathing ambient air or significant clinical symptoms that require hospital admission.
- 6 Patients had to be enrolled within 10 days of disease onset.
- 7 Not part of any other clinical trial and agrees not to participate in any.

#### 4.2 Exclusion Criteria

- 1 Patients who are pregnant or breastfeeding.
- 2 Will be transferred to a non-study site hospital or discharge from hospital within 72 hours.
- 3 Known sensitivity/allergy to hydroxychloroquine or Favipiravir
- 4 Current use of hydroxychloroquine for another indication
- 5 Prior diagnosis of retinopathy
- 6 Prior diagnosis of glucose-6-phosphate dehydrogenase (G6PD) deficiency
- 7 Major comorbidities increasing the risk of study drug including: i. Hematologic malignancy, ii. Advanced (stage 4-5) chronic kidney disease or dialysis therapy, iii. Known history of ventricular arrhythmias, iv. Current use of drugs that prolong the QT interval, Severe liver damage (Child-Pugh score  $\geq$  C, AST > 5 times the upper limit), HIV.
- 8 The investigator believes that participating in the trial is not in the best interests of the patient, or the investigator considers unsuitable for enrollment (such as unpredictable risks or subject compliance issues).
- 9 Clinical prognostic non-survival, palliative care, or in deep coma and no have response to supportive treatment within three hours of admission
- 10 Patient with irregular rhythm or the QTc (corrected QT interval) in the baseline ECG more than 490ms.

- 11 Patient with a history of heart attack (myocardial infarction)
- 12 Patient with a family history of sudden death from heart attack before the age of 50
- 13 Take other drugs that can cause prolonged QT interval
- 14 Patient who is receiving immunosuppressive therapy (cyclosporin) which cannot be switched to another agent or adjusted while using the investigational drug
- 15 Gout/history of Gout or hereditary xanthinuria or xanthine calculi of the urinary tract.
- 16 Serum uric acid level > 2 times upper level of normal associated with symptoms of gout

### 4.3 Patient recruitment

In the participating centers, daily notification from the microbiology laboratory for the new positive cases to the research coordinators. Then assessment of the eligibility would be done.

## 5. PREMATURE DISCONTINUATION OF THE STUDY

Premature discontinuation of the trial would be based on the decision of DSMB or the investigator initiated based on the following:

- Adverse event: clinical or laboratory event that in the medical judgment of the investigator, for the best interest of the patient are grounds for discontinuation
- Major deviation from the protocol: the patient's findings or conduct failed to adhere to the protocol requirements.
- Other reason: e.g., administrative problem such as termination of study by the sponsor.

## 6. TREATMENTS

### 7.1 Description of investigational drug and reference therapy

### 7.2 Packaging and labelling

Table 2 Packaging and labelling of the study medications

| Generic Name             | Favipiravir                                                                        | Hydroxychloroquine                                                   |
|---------------------------------|-------------------------------------------------------------------------------------------|-----------------------------------------------------------------------------|
| Trade Name               | Avigan®                                                                                   | Plaquenil®                                                                  |
| Dosage Form              | Tablet                                                                                    | - Tablet
- Suspension (extemporaneous preparation) manufactured in house |
| Tablet Strength          | 200 mg                                                                                    | - 200 mg
- 25 mg/mL for suspension formulation                           |
| Appearance and Packaging | Light-yellow, film-coated round tablet
Boxes of 100 tablets in press through packaging | White to off white, film coated tablet
Bottle of 100 tablets             |
| Manufacturer             | FujiFilm Toyama Chemical Co.                                                              | Concordia Pharmaceuticals Inc                                               |
| Supplier                 | Satellite pharmacy                                                                        | Satellite pharmacy                                                          |

-Both drugs are available in oral dosage form (oral tablet). Hydroxychloroquine is also available as suspension that is manufactured at King Abdulaziz Medical City outpatient compounding pharmacy.

#### Reference Therapy:

Standard of care is defined as: Treatment that is accepted by medical experts as a proper treatment for Covid-19 disease. Standard care comprised, as necessary, supplemental oxygen,

noninvasive and invasive ventilation, antibiotic agents, vasopressor support, renal-replacement therapy, extracorporeal membrane oxygenation (ECMO), and antiviral therapy except Favipiravir. Also, it may include intravenous fluids and medications for symptoms relieve.

Although it would not be preferred to use medication that has antiviral activity, the treating physician would have the authority/ autonomy to start the patient on antiviral but not Favipiravir, i.e., Lopinavir–Ritonavir, interferon, ribavirin, Hydroxychloroquine or Remdesivir). Anyone of those medications with possible antiviral activity against SARS-CoV-2 would be accepted to be used in the case that treating physicians thought it would be the best of interest for the patient.

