## 2.4 Secondary Endpoint

1. Clinical status assessed by the seven-category ordinal scale.
2. The requirement of ICU admission or Mechanical ventilation
3. 28- and 90-days mortality.
4. PCR test negative conversion rate and days from positive to negative\*\*
5. Evaluate the safety of investigational therapeutics as compared to the control arm.
6. Length of hospital stay.
7. Duration of fever.
8. QT prolongation (Daily follow up during the concomitant use of both medications and regularly till Day14)

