### 7.3 Safety monitoring

Site PI should follow on a daily basis all the possible AEs while using the investigational medications and up to day-14. This includes regular monitoring of hematology and blood chemistry. Daily ECG and QT interval monitoring. And LFT every other day. In case of any concerns that might require holding/stopping medication, causality assessment should be done by PI and with a consultation to an independent clinician.

Details of cardiac toxicity monitoring as follow:

1. A baseline ECG before starting then daily ECG after.
2. Daily ECG to be done through day 1-10 or twice daily if the corrected QT interval more than 480ms.
2. Maintain serum level of Mg>1.0 meq, and K>4.5 meq throughout the 10 days of therapy.
3. If the QTc prolonged more than 500ms after starting, stop the medication.
4. Avoid any other QT prolong medication during the regimen.
5. If the patient develops torsades de-pointes, stop the medication immediately, follow ACLS protocol and call the cardiologist on-call.

If you have any query or help, please call for cardiology team in you center.

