| Laboratory data collection               |              |                 |    |     |    |     |    |     |     |     |     |          |
| Covid-19 PCR from Respiratory sample *          | X            | X               |    |     | X  |     |    | X   |     | X   | X   | X        |
| CBC, renal profile and LFT on Study Drug | X            | X               | X  | X   | X  | X   | X  | X   |     | X   | X   |          |
| CBC, renal profile and LFT on SoC        | X            | X               |    |     | X  |     |    | X   |     |     | X   |          |

|                                             |   |   |   |   |   |  |  |   |  |  |  |  |
|---------------------------------------------|---|---|---|---|---|--|--|---|--|--|--|--|
| ECG for patient on Study Drug | X | X | X | X | X |  |  | X |  |  |  |  |
| ECG for patient on SoC        | X | X |   |   | X |  |  | X |  |  |  |  |

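### Controls may receive hydroxychloroquine, but the ECG schedule is set by arm: 1 or 2 scheduled ECGs during an assumed 5-day course, against 5 in the experimental arm

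*Protocol*

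**What the plan says.** **Control treatment.** The Reference Therapy text bars only favipiravir. It discourages other antivirals ("Although it would not be preferred to use medication that has antiviral activity") but leaves the choice to the treating physician and accepts any of the listed agents, among them "interferon, ribavirin, Hydroxychloroquine or Remdesivir". Section 1.5 adds that national guidelines recommended hydroxychloroquine at the time.

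**QT risk.** Sections 1.4, 1.5.5.1 and 10.2 attribute QTc prolongation to hydroxychloroquine. The favipiravir reaction lists in Sections 1.5.5.1 and 10.2 do not mention QT.

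**ECG schedule.** Table 4 has two ECG rows. "ECG for patient on Study Drug" is marked at D0, D1, D2, the unnumbered column between D2 and D5, D5 and D10. "ECG for patient on SoC" is marked at D0, D1, D5 and D10.

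**QTc rules.** Section 7.3 (Safety monitoring) sets the frequency, "Daily ECG to be done through day 1-10 or twice daily if the corrected QT interval more than 480ms", and the stop rule, "If the QTc prolonged more than 500ms after starting, stop the medication". It also says "Avoid any other QT prolong medication during the regimen". The section opens with adverse events during use of the investigational drugs and sets its electrolyte targets for a 10-day course. Item 8 of Section 2.4 describes QT monitoring as "Daily follow up during the concomitant use of both medications and regularly till Day14".

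**The concern.** On the protocol's own account of risk, hydroxychloroquine is the drug that calls for close ECG follow-up. The protocol permits that drug in both arms but writes the intensive schedule for one. Two patients on the same drug could then be monitored differently because of their allocation and not their exposure.

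The first consequence is for patient safety: symptom-free QTc prolongation in a control could go unseen until the next scheduled ECG. The second is inconsistency. Section 7.3 can be read by exposure or by arm, so one site may stop hydroxychloroquine at 500 ms in a control while another sees no protocol rule to apply. A lesser consequence is that QT prolongation is a secondary endpoint, so unequal ECG schedules also mean unequal ascertainment between the arms.

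**Working it through.** There is no stated figure to reproduce. The check counts the scheduled ECG days that fall inside a hydroxychloroquine course.

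**Inputs**
- Standard-of-care ECG days (Table 4): D0, D1, D5, D10.
- Experimental ECG days during hydroxychloroquine: D1 to D5 daily. This reads the unnumbered column between D2 and D5 as D3 and D4, which agrees with the daily rule in Section 7.3.
- Course length: 5 days, as for the experimental arm (Section 7.2, Treatment Period). This is an assumption for controls, because the protocol fixes no dose, duration or start day for them.

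**Count.** For a start on day s, the course covers days s to s+4. The number of scheduled ECGs is the number of standard-of-care ECG days in that window.

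| Control start | ECG days in the course | Scheduled ECGs | Course days without one | First scheduled ECG, by course day |
|---|---|---|---|---|
| D1 | D1, D5 | 2 | 5 − 2 = 3 | 1 |
| D2 | D5 | 1 | 5 − 1 = 4 | 4 |
| D3 | D5 | 1 | 4 | 3 |
| D4 | D5 | 1 | 4 | 2 |
| D5 | D5 | 1 | 4 | 1 |
| D6 | D10 | 1 | 4 | 5 |
| D7 | D10 | 1 | 4 | 4 |
| D8 | D10 | 1 | 4 | 3 |
| D9 | D10 | 1 | 4 | 2 |
| D10 | D10 | 1 | 4 | 1 |

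A D0 start would also give 2 (D0 and D1). A start on D11 or later would give none.

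**Experimental arm.** Hydroxychloroquine on D1 to D5 has 5 scheduled ECGs, with 0 of 5 days uncovered. If the unnumbered column meant a single ECG, the count would be 4.

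**Scope of Section 7.3.** Some lines name no arm and could be applied to anyone starting the drug, such as the baseline-then-daily ECG instruction and the 500 ms rule. Others point to the experimental course: the opening reference to the investigational drugs, the 10-day electrolyte targets and the mention of the regimen. The QT endpoint ties daily follow-up to taking both drugs together, which a control does not do. If Section 7.3 is read as covering controls on hydroxychloroquine, it conflicts with their row in Table 4. If it is not, they have no QTc rule. Either way the text needs to say which.

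Section 7.3 asks for daily ECGs to day 10, whereas the study-drug row of Table 4 shows none between D5 and D10. That separate mismatch does not alter the D1 to D5 count.

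**The case against.** The strongest case against is that the protocol can be read by exposure. The Table 4 row refers to patients on study drug, hydroxychloroquine is listed in that table as a study drug, and the cardiac rules in Section 7.3 name no arm. This is a fair reading of those lines, but the separate standard-of-care row contradicts it and is the more explicit instruction for a control.

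A second argument is that other protections exist:
- The exclusions in Section 4.2 apply to both arms. They cover baseline QTc above 490 ms, ventricular arrhythmia, previous infarction, a family history of sudden death, and other QT-prolonging drugs.
- Section 1.4 warns against combining hydroxychloroquine with other QT-prolonging drugs.
- Assessments follow in-house policies (Section 7), side effects are assessed daily, and the treating physician may stop medication (Section 7.1).
- The grading appendix makes a QTc of 501 ms or more Grade 3, and the monitoring board sees unblinded safety data (Section 12.2).

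These lower the risk, and clinicians may order ECGs beyond the schedule. None of them sets an on-treatment ECG frequency or a QTc stop threshold for such a control.

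Third, the untested combination could justify closer follow-up in the experimental arm, since Section 1.4 reports no data on favipiravir's effect on hydroxychloroquine levels. That is a reasonable motive for extra caution. However, the same section concludes, by extrapolation, that there is no clear accumulation risk, and the motive does not explain leaving the single drug without a stated QTc rule.

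Finally, the counts depend on a borrowed course length, and use in controls is discouraged and of unknown frequency. Both points stand. They limit what can be said about size but do not remove the gap.

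**Conclusion.** The concern holds. The protocol allows a drug to which it attributes QTc prolongation in the control arm, schedules control ECGs without regard to that use, and leaves it unclear whether the daily ECG, 480 ms and 500 ms rules apply. For an assumed 5-day course, a control has 2 scheduled ECGs with a D1 start and 1 with any start from D2 to D10, against 5 for the experimental arm (4 if the unnumbered Table 4 column means one ECG). The first scheduled ECG on the drug can fall as late as course day 5, for a D6 start.

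These figures concern scheduled study ECGs only. The protocol gives no rate of hydroxychloroquine use in controls, so the number of patients affected is not estimated. This is an inexpensive safety clarification that should be made; it does not affect the primary analysis.

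**What to change.** State in Section 7.3 (Safety monitoring) that the cardiac rules apply to any participant in either arm while receiving hydroxychloroquine: daily ECG, twice daily when QTc exceeds 480 ms, and stopping when it exceeds 500 ms. Footnote or relabel the ECG rows of Table 4 to match, so that a control given the drug has daily ECGs from the day it is started.

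The rule should run from the start of the drug and not from study day. Daily ECGs on D1 to D10 would cover all 5 days of a course begun by D6, but only 4 days of one begun on D7 and 1 day of one begun on D10.

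The cost is one sentence, one footnote and some additional ECGs in controls given the drug: 5 − 2 = 3 more for a D1 start, or 5 − 1 = 4 more for a start from D2 to D10, per assumed course.

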### 7.3 Treatment assignment

In the participating site, the research coordinator/ principal investigator for the site will check all positive reported COVID-19 by PCR confirmed SARS-coV-2 viral infection. Then an assessment of the eligibility by the research coordinator and assessing inclusion/exclusion criteria. The possible study participant can be assessed in the first 72 hours of admission regarding eligibility. Once eligible, informed consent will be obtained. Randomization will be done in 1:1 whether to intervention or control arm and stratified by the center.

### 7.4 Randomization

Eligible participants will be randomized in a 1:1 ratio to either the combination group (Favipiravir and Hydroxychloroquine) or a control group. Randomization will be stratified by clinical site.

The patients will be randomized utilizing Web based data entry System. The sequence of treatment assignment will be determined prior to the start of the study.

### 7.5 Storage conditions

Table 3 Storage Conditions for study medications

| Drug | Favipiravir | Hydroxychloroquine |
|------|-------------|--------------------|
|------|-------------|--------------------|

|                          |                                                         |                                                                                                               |
|--------------------------|---------------------------------------------------------|---------------------------------------------------------------------------------------------------------------|
| Storage Condition | Storage at room temperature [20° to 25°C (68° to 77°F)] | Store at room temperature [20° to 25°C (68° to 77°F), allows excursions between 15° and 30°C (59° and 86°F)]. |
| Stability         | Must be dispensed in a tight container                  | Must be dispensed in a tight, light-resistant container to keep ingredients active until expiry date          |

### 7.6 Treatment compliance

Compliance with the study drug will be assessed by the study coordinator at each study visit and he / she will be required to record in the CRF any missed dose, the reason for missing doses, any adverse effect, and any associated issues, beginning from visit 1.

### 7.7 Accountability and Destruction

In compliance with the International Conference on Harmonization (ICH) guidelines, Title E6-Good Clinical Practices section 4.6, and CFR 21 Part 312.61, the Investigator is responsible for maintaining records reflecting the receipt and dispensation of the investigational product. Additionally, the Investigator must comply with any local regulations regarding the proper documentation of study drug accountability.

The study drug must be stored and handled in accordance with the Sponsor's instructions.

At the end of the study, remaining therapeutic unit will be destroyed locally and a certificate of destruction will be issued by King Abdulaziz Medical City.

## 7. PROCEDURES AND ASSESSMENTS

The Study comprises of three major parts Screening, Treatment and Follow-up period. Each Part consists of specified procedures to be done and assessments to be carried. All study procedures will be conducted in King Abdul-Aziz Medical City National Guard Health Affairs in Riyadh. The investigator and supporting study team will be responsible to document all the procedures and assessments done in the appropriate source document and the patient e CRFs. All procedures and assessments will support the safety and validity of conclusions drawn from the study protocol. Procedures and assessments such as vital signs, laboratory tests...etc will follow in-house policies and guidelines. When multiple assessments are taken at the same time point, the most out-of-range value shall be considered

### 7.1 Screening/Baseline

In the participating site, the research coordinator/ delegated study personnel for the site will check all positive reported COVID-19 by PCR confirmed SARS-coV-2 viral infection. Then an assessment of the eligibility by the research coordinator and assessing inclusion/exclusion criteria. The possible study participant can be assessed in the first 72 hours of admission regarding eligibility. Once eligible, informed consent will be obtained. Randomization will be done in 1:1 whether to intervention or control arm and stratified by the center.

Daily assessment and data reporting will be done by the research coordinator/ delegated study personnel including the side effect using the included CRF.

While the management will be done by the treating physician and even stopping the medication in case of concerns. Stopping the interventional medication need to be justified; where a form would be filled.

### 7.2 Treatment Period

The treatment intervention would be for a maximum of 10 days from randomization and it would be as follow:

Favipiravir for 10 days as follow:

Administer 1800 mg (9 tablets) by mouth twice daily for one day, followed by 800mg (4 tablets) twice daily (total days of therapy is 10 days)

Hydroxychloroquine for 5 days:

(400mg) twice daily on day 1; for days 2-5 (200mg) twice daily.

### 7.3 Safety monitoring

Site PI should follow on a daily basis all the possible AEs while using the investigational medications and up to day-14. This includes regular monitoring of hematology and blood chemistry. Daily ECG and QT interval monitoring. And LFT every other day. In case of any concerns that might require holding/stopping medication, causality assessment should be done by PI and with a consultation to an independent clinician.

Details of cardiac toxicity monitoring as follow:

1. A baseline ECG before starting then daily ECG after.
2. Daily ECG to be done through day 1-10 or twice daily if the corrected QT interval more than 480ms.
2. Maintain serum level of Mg>1.0 meq, and K>4.5 meq throughout the 10 days of therapy.
3. If the QTc prolonged more than 500ms after starting, stop the medication.
4. Avoid any other QT prolong medication during the regimen.
5. If the patient develops torsades de-pointes, stop the medication immediately, follow ACLS protocol and call the cardiologist on-call.

If you have any query or help, please call for cardiology team in you center.

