## 8. FLOW CHART

Table 4: Flow Chart

|                                                 | Study period |                 |    |     |    |     |    |     |     |     |     |          |
|-------------------------------------------------|--------------|-----------------|----|-----|----|-----|----|-----|-----|-----|-----|----------|
|                                                 | Baseline     | Post allocation |    |     |    |     |    |     |     |     |     | Closeout |
| Timepoint study days                            | D0           | D1              | D2 | D'' | D5 | D'' | D9 | D10 | D'' | D14 | D21 | D28      |
| Enrolment and assignment                 |              |                 |    |     |    |     |    |     |     |     |     |          |
| Eligibility assessment                          | X            | X               |    |     |    |     |    |     |     |     |     |          |
| Informed consent                                | X            | X               |    |     |    |     |    |     |     |     |     |          |
| Randomization                                   | X            | X               |    |     |    |     |    |     |     |     |     |          |
| Baseline data                                   | X            | X               |    |     |    |     |    |     |     |     |     |          |
| Study drug administration                |              |                 |    |     |    |     |    |     |     |     |     |          |
| Favipiravir                                     |              | X               | X  | X   | X  | X   | X  | X   |     |     |     |          |
| Hydroxychloroquine                              |              | X               | X  | X   | X  |     |    |     |     |     |     |          |
| Adverse effect reaction                         |              | X               | X  | X   | X  | X   | X  | X   | X   | X   |     |          |
| Serious adverse event assessment                |              | X               | X  | X   | X  | X   | X  | X   | X   | X   | X   | X        |
| Clinical data collection                 |              |                 |    |     |    |     |    |     |     |     |     |          |
| Seven-category ordinal scale and CRF            | X            | X               | X  | X   | X  | X   | X  | X   | X   | X   | X   | X        |

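### Section 7.3 requires a daily ECG on D1–D10, but Table 4 schedules none for study-drug patients on D6–D9 while favipiravir continues, and none after D10 although QT is an endpoint to Day 14

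*Protocol*

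**What the plan says.** Section 7.3 (Safety monitoring) gives numbered cardiac rules for patients on the study drugs. After a baseline ECG, monitoring is daily: "Daily ECG to be done through day 1-10 or twice daily if the corrected QT interval more than 480ms". The action rule is "If the QTc prolonged more than 500ms after starting, stop the medication". The electrolyte rule covers the same span: "Maintain serum level of Mg>1.0 meq, and K>4.5 meq throughout the 10 days of therapy".

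Section 7.2 (Treatment Period) gives the exposure: "The treatment intervention would be for a maximum of 10 days from randomization", with favipiravir for 10 days and hydroxychloroquine for 5.

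Table 4 in section 8 has separate ECG rows for the two arms, each beginning "ECG for patient on". After baseline, the study-drug row is marked at D1, D2, the first D'' column, D5 and D10. The standard-of-care row is marked at D1, D5 and D10. Neither row has a mark after D10. Under "Study drug administration", favipiravir is marked in every column from D1 to D10.

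Section 2.4, endpoint 8, is QT prolongation, to be followed daily while both drugs are given and then at regular intervals, not further specified, until Day 14.

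**The concern.** The protocol contains three ECG schedules that do not agree: section 7.3, Table 4 and endpoint 8. The disagreement falls on a rule meant to protect patients. The 480 ms step-up and the 500 ms stop can act only on a recorded ECG, and the visit schedule provides none on four of the ten treatment days. An analysis plan cannot recover an ECG that was not taken.

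Section 4.2 adds to this. It excludes only a baseline QTc above 490 ms, so a patient can enter between 480 and 490 ms, already in the range where section 7.3 wants two ECGs a day. Table 4 gives that patient none on D6–D9.

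For endpoint 8 the issue is data. Follow-up to Day 14 is promised, but nothing is scheduled in either arm after D10.

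**Working it through.** The protocol states no figure to reproduce here, so the check compares schedules.

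**1. The schedules side by side** (D'' read as the days between its neighbours):

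| | D1 | D2 | D'' | D5 | D'' | D9 | D10 | D'' | D14 |
|---|---|---|---|---|---|---|---|---|---|
| Section 7.3 ECG, study drug | X | X | X | X | X | X | X | | |
| Table 4 ECG, study drug | X | X | X | X | – | – | X | – | – |
| Table 4 ECG, standard of care | X | – | – | X | – | – | X | – | – |
| Table 4 favipiravir | X | X | X | X | X | X | X | | |
| Table 4 hydroxychloroquine | X | X | X | X | – | – | – | | |

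The study-drug ECG row has 12 cells under 12 column headings. The standard-of-care ECG marks from D0 to D10 fall in the same columns as the standard-of-care laboratory marks. The blanks are therefore not a shifted or broken row.

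**2. Count of on-treatment ECG days.** Section 7.3 gives 10 (D1–D10). Table 4 gives 6 (D1–D5 and D10). The difference, 10 − 6 = 4, is D6, D7, D8 and D9. The gap does not depend on how D'' is read, because the second D'' column and D9 are both blank.

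**3. Delay under Table 4.** The next marked ECG after D5 is D10, so delay = 10 − onset day. For onset on D6, D7, D8 or D9 the delay is 4, 3, 2 or 1 days.

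**4. Share never seen.** An episode starting on day s and lasting d days is seen at D10 only if s + d − 1 ≥ 10. Assume onset is spread evenly over D6–D9:
- d = 1: no onset day qualifies, so 100% are missed.
- d = 2: only s = 9 qualifies, so 75% are missed.
- d = 3: s = 8 and 9 qualify, so 50% are missed.
- d = 4: s = 7, 8 and 9 qualify, so 25% are missed.

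Under section 7.3 none would be missed.

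**5. Patients in the window.** The protocol gives no such figure. Assume exponential time to improvement, every improvement counted as a discharge that ends favipiravir, and no deaths or early stops. The number still on favipiravir is then 260 × 0.5^(t/median).
- Median 7.7 days (the planned effect): 260 × 0.5^(6/7.7) ≈ 151 at D6 and 260 × 0.5^(9/7.7) ≈ 116 at D9.
- Median 11 days (no effect): about 178 at D6 and 147 at D9.

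**6. Endpoint 8.** Table 4 is daily on D1–D5, which fits the first part of the endpoint. After that it has one ECG, at D10, and none on D11–D14.

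**7. Unequal frequency between arms.** Post-baseline laboratory days are 12 (D1–D10, D14, D21) against 4 (D1, D5, D10, D21). ECG days are 6 against 3. Section 9.4 compares Grade 3 or higher AEs with Fisher's exact test, and section 10.1 lets an abnormal laboratory finding count as an AE. Assume 260 per arm all remaining under observation, equal true risk, 20% of patients with some other Grade 3 or higher AE, and abnormalities starting evenly over D1–D10. Study-drug labs then detect every abnormality. Control labs detect 30%, 50% and 70% of those lasting 1, 2 and 3 days. The probability of a false rejection at 0.05 is:

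| Assumed lab risk | 1 day | 2 days | 3 days |
|---|---|---|---|
| 1.8% | 4.7% | 4.3% | 4.0% |
| 5% | 9.9% | 6.8% | 4.9% |
| 10% | 27.8% | 15.5% | 7.9% |

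The 1.8% is the protocol's own rate for neutrophil decrease and AST increase on favipiravir, given without grade (section 10.2). At that rate the test stays below 5% throughout. The higher risks are assumptions with no source in the protocol.

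**The case against.** The strongest reply is pharmacological. Sections 1.4, 1.5.5.1 and 10.2 name QTc prolongation for hydroxychloroquine and do not list it for favipiravir. Hydroxychloroquine stops on D5, and Table 4 is daily exactly while it is given. This stands, and it limits the risk. A reader might infer that patients would take up to 8 further favipiravir doses (two a day for four days) into a drug-induced QT problem. The document gives no basis for a QT effect of favipiravir. What the reply does not do is reconcile the texts, since section 7.3 sets both its ECG and its electrolyte rules for ten days.

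Secondly, section 7.3 binds sites whatever Table 4 shows, and Table 4 could be read as a recording schedule. That is fair: the delays in the working apply only where a site follows the table and no ECG is taken for clinical reasons. But section 7.4 (Follow-up Period) sends sites to the flow chart for other laboratory investigations, and the ECG rows stand in that block, so reliance on the table is plausible.

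Two further inferences should not be drawn:
- **LFT frequency.** Section 7.3 says "And LFT every other day", while the row beginning "CBC, renal profile and LFT on" is marked on adjacent days in the study-drug arm. The table asks for more than the text, so no monitoring is lost. At most the wording needs aligning.
- **Grade 3 or higher AEs.** The unequal schedules do not show that this comparison is invalid. The tilt needs brief abnormalities, risks above those the protocol cites, and little unscheduled testing in control patients. Section 9.4 makes AE analysis mainly descriptive and promises a detailed analysis plan, where a sensitivity analysis would belong.

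**Conclusion.** The inconsistency is real, sits in current text and should be corrected. Section 7.3 requires ECGs on four treatment days for which Table 4 schedules none, and endpoint 8 runs four days past the last scheduled ECG. For a site working from Table 4, a QTc excursion arising on D6–D9 is first scheduled to be seen 1 to 4 days late, and one that ends before D10 is not seen at all. The delay follows from the table alone. The missed shares assume evenly spread onset, and the patient numbers assume exponential improvement with discharge.

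The clinical risk is limited, for the reasons given under the objection. The difference in testing frequency between arms (labs 12 v 4 days, ECGs 6 v 3) is no more than a caution when reading the AE comparison.

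**What to change.** - **Table 4, study-drug ECG row:** mark every day from D1 to D10, in line with section 7.3. This is 4 ECGs per patient, at most 4 × 260 = 1,040, all already required by section 7.3.
- **Table 4, both ECG rows:** add D14, so that endpoint 8 can be assessed as stated. This is at most 520 ECGs. D14 is already a column with a respiratory PCR sample. Shortening endpoint 8 to D10 is not recommended: it would trim a stated safety follow-up, and section 7.3 follows AEs to Day 14.
- **LFT wording:** align section 7.3 with Table 4 if the protocol is being amended anyway.

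There is one side effect. Post-baseline ECG days become 11 on study drug (10 + 1) against 4 on standard of care (3 + 1), compared with 6 against 3 now. If the trial team wants to guard the AE comparison, an analysis limited to days scheduled in both arms can go in the statistical analysis plan. The planned Fisher test need not change.
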